## Abstract

**Background:**

The additional use of radiotherapy has changed the treatment of locally advanced rectal cancer (LARC) dramatically. But a major achievement has been the development of total mesorectal excision (TME) as a surgical standard and the recognition that the surgeon is the predominant prognostic factor. The benefit of preoperative hypofractionated radiotherapy (SCRT; five fractions each of 5 Gy), initially established by the Swedish Rectal Cancer Trial, has been demonstrated in conjunction with TME by the Dutch Colorectal Cancer Group. The concept of combined neoadjuvant radiochemotherapy (conventional radiation of about 50 Gy with chemotherapy) has not been compared over surgery alone with TME. However, the German Rectal Cancer Study Group recently demonstrated that preoperative radiochemotherapy (RCT) was better than postoperative radiochemotherapy in terms of local control.

**Methods and design:**

Patients with histological proven rectal cancer staged T2N+ or T3 are randomized to receive either SCRT (25 Gy in five fractions of 5 Gy) plus TME-surgery within 5 days or RCT (50.4 Gy in 28 fractions of 1.8 Gy, continuous infusion 5-fluorouracil) plus TME-surgery 4–6 weeks later. All patients receive adjuvant chemotherapy (12 weeks continuous infusional 5-FU) and are followed up for 5 years. TME-quality is independently documented by the surgeon and the pathologist. Hypothesis of the study is that RCT is superior to SCRT in terms of local recurrence after five years. Secondary endpoints are overall survival, disease-free survival, complete resection rate (R0 resection), rate of sphincter saving resection, acute and late toxicity (radiation related side effects), and quality of life (including long term bowel function).

**Discussion:**

Similar long-term survival, local control and late morbidity have been reported for both concepts of preoperative therapy in non-comparative studies. In addition to other ongoing (and recently published) comparative trials we include a larger number of patients for adequate power, apply quality-controlled TME and try to avoid the adjuvant treatment bias by mandatory adjuvant chemotherapy in both groups. Further more, stratification of the initially planned surgical procedure and sphincter-preservation will generate valid evidence whether RCT will allow a less aggressive (sphincter saving) surgical approach.

## Background

Colorectal cancer (CRC) is the second most frequent malignant disease in western countries. In Germany, more than 70,000 new cases occur yearly and approximately 40% are located in the rectum [1]. Despite major efforts in prevention/screening and significant improvements in surgical, radiation and medical therapy CRC is still one of the leading causes of cancer mortality.

Besides survival, a major problem in locally advanced rectal cancer (LARC) is the thread of local recurrence, not only because of the limited therapeutic options but especially because of the impaired quality of life due to the intense pain and uncontrolled soiling (caused by faecal incontinence and/or mucus/blood from the tumour).

The last decade has brought advances in multimodality treatment of LARC. After the endorsement of postoperative adjuvant radiochemotherapy by a National Cancer Institute Consensus Conference in 1990 [2], several randomized studies reported lower rates of local failure with preoperative radiotherapy than with surgery alone [3,4]. Furthermore, the Swedish Rectal Cancer Trial, evaluating preoperative short-course radiotherapy (SCRT), found an advantage in overall survival compared to surgery alone [5]. The recently published results from the CAO/ARO/AIO-94 trial report that preoperative combined radiochemotherapy (RCT) is superior to postoperative RCT in terms of outcome [6]. A major achievement in the treatment of LARC has been the development of total mesorectal excision (TME) as a surgical standard [7]. So far, the only study evaluating preoperative therapy together with a documented quality controlled TME-surgery is the Dutch Colorectal Cancer Group study. SCRT with TME was superior to TME alone in terms of local recurrence, whereas overall survival was similar in both groups [4]. The EORTC 22921 trial, already started in the late nineties of the last century and published recently, showed a similar reduction in local recurrence whether 5FU/leucovorin chemotherapy was given with pre-operative radiotherapy, after preoperative radiotherapy plus surgery, or both [8].

In Europe, there is still much debate about the two different approaches to preoperative therapy – SCRT and "long-course" RCT. Although having undoubted weakness, a recently published study of the Polish Colorectal Study Group comparing the two approaches reported no superiority for RCT in terms of either overall or local control [9]. Even in the U.S., there is now increasing demand in considering the use of SCRT in order to better stratify for adjuvant therapy, because of the low probability of downsizing and therefore "unchanged" initial TN-staging [10].

Our study, the Berlin Rectal Cancer Trial (BRCT) was planned in 2003 and enrolled the first patient in 2004. After initiation of the polish trial and the BRCT in Europe, a comparative trial very similar to the BRCT was conducted in Australia. This TROG/AGITG trial recently closed recruitment after enrolling some three hundred patients. In addition to the recently published polish trial we include a larger number of patients for adequate power, applied quality-controlled TME and tried to avoid the adjuvant treatment bias by mandatory adjuvant chemotherapy in both groups. Further more, stratification of the initially planned surgical procedure and sphincter-preservation will generate valid evidence whether RCT will allow a less aggressive (sphincter saving) surgical approach.

Hypothesis of our study is that RCT is superior to SCRT in terms of local recurrence after five years.

## Methods and design

### Study design

The study is a two-arm prospective randomised multicentre trial. The treatment algorithm is depicted in Figure 1.

**Figure 1 F1:**
[figure not shown]
**Treatment algorithm**.

### Study objectives

The study compares the value of the two most common preoperative therapy regimens in LARC in terms of local recurrence. The primary outcome measure is local recurrence after a follow up of five years. The secondary outcome measures are overall survival, disease-free survival and quality of life (including long term bowel function) after a median follow-up of five years. Further more, secondary endpoints are the complete resection rate (R0 resection) and the rate of sphincter saving resection, both analysed after surgery of the last patient recruited. Acute and late toxicity (radiation related side effects) will be observed after a median follow-up of five years.

### Coordination

The trial is coordinated by the clinical trial office of the Charité Comprehensive Cancer Center, Charité, Berlin. The clinical trial office is responsible for overall trial management, trial registration (EudraCT Number 2004-001606-27; Current Controlled Trials ISRCTN56463377), database management, quality assurance including monitoring, reporting and for the scientific program of all trial related meetings supported by the Berliner Krebsgesellschaft e.V..

### On-site monitoring

During recruitment of patients monitoring on site is performed according to good clinical practice (GCP) guidelines. The data management will be performed by the clinical trial office of the Charité Comprehensive Cancer Center, Charité, Berlin.

### Ethics, informed consent and safety

The final protocol was approved by the ethics committee of the Charité, Berlin, Germany (ref: AA3/03/38). It is certified and recommended by the German Cancer Society (Deutsche Krebsgesellschaft e.V., "Gütesiegel A", 29th September 2003). This study complies with the Helsinki Declaration in its recent version, the Medical Association's professional code of conduct, the principles of Good Clinical Practice (GCP) guidelines and the Federal Data Protection Act. The trial will also be carried out in keeping with local legal and regulatory requirements. The medical secrecy and the Federal Data Protection Act will be followed. Written informed consent is obtained from each patient in oral and written form before inclusion in the trial and the nature, scope, and possible consequences of the trial have been explained by a physician. The investigator will not undertake any measures specifically required only for the clinical trial until valid consent has been obtained.

### Statistics

Local recurrence after five years follow up has been chosen as primary endpoint. Survival in the regarded treatment arms will be graphically demonstrated by using Kaplan-Meier estimates. Univariate Log-Rank tests as well as multivariate Cox' regression analyses will be conducted for the analysis of primary and secondary endpoints. The alteration of hazard ratios in time will be modelled [11]. Proving a two-sided hypothesis of differences between the treatment arms, the calculation of the sample size of the trial was based on expected local recurrence rates of 12% in the SCRT arm compared with 7% in the RCT arm, resulting in altogether 760 patients (Log-Rank-test, base time: 5 years, accrual time: 6 years, follow-up: 5 years, proportion loss to follow-up: 10% per arm, error of the 1^st ^kind: α = 5% two-sided, power = 80%). An interim analysis is planned after five years study time with an error of the 1^st ^kind = α_int _= 0.5% [12].

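### The sample size makes no stated allowance for death without local recurrence, and Kaplan-Meier is the only estimator named although death competes with the primary endpoint

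*Protocol article*

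**What the plan says.** The Study objectives section states that "The primary outcome measure is local recurrence after a follow up of five years", and the Statistics section repeats it: "Local recurrence after five years follow up has been chosen as primary endpoint". Death is not part of this endpoint. Overall survival and disease-free survival are separate secondary endpoints.

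On estimation, the sentence right after the endpoint in the Statistics section reads "Survival in the regarded treatment arms will be graphically demonstrated by using Kaplan-Meier estimates". On testing, the next one reads "Univariate Log-Rank tests as well as multivariate Cox' regression analyses will be conducted for the analysis of primary and secondary endpoints".

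The sample size rests on "expected local recurrence rates of 12% in the SCRT arm compared with 7% in the RCT arm", "resulting in altogether 760 patients", with "base time: 5 years, accrual time: 6 years, follow-up: 5 years", two-sided α of 5%, power of 80% and "proportion loss to follow-up: 10% per arm". The list has no death rate. Nothing in the article says how a death without local recurrence is handled, whether the 12% and 7% already allow for deaths, or whether the 10% loss includes them.

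**The concern.** A patient who dies without local recurrence can no longer have one. This matters in two places.

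- **Planning.** Deaths remove patients from risk, so fewer recurrences will be seen than a calculation without deaths predicts. Power depends on the number of recurrences. The article presents adequate power as an advantage over an earlier comparative trial.
- **Reporting.** If deaths are censored and recurrence is shown as 1 minus Kaplan-Meier, the curve estimates the recurrence rate in a population where nobody dies. That is higher than the share of patients who actually recur. The hypothesis concerns recurrence after five years, so the 5-year rates and their difference are the figures that readers will take away.

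**Working it through.** **Inputs from the Statistics section:** 12% v 7% at 5 years, 760 patients, 6 years' accrual plus 5 years' follow-up, 10% loss, two-sided α 5%.

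**Assumptions:** 1:1 allocation (380 per arm); constant hazards; uniform accrual, so each patient is followed for 5 to 11 years; loss acting as a hazard that reaches 10% by year 5; 5-year probability of death without recurrence m = 10%, 20%, 30% or 40%, equal in both arms. The values of m are mine.

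**Step 1. Hazards.** SCRT: λ₁ = −ln(0.88)/5 = 0.02557. RCT: λ₂ = −ln(0.93)/5 = 0.01451. HR = 0.568. Loss: c = −ln(0.90)/5 = 0.02107. Death: d = −ln(1−m)/5.

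**Step 2. Reproduce the plan with d = 0.** With L = λ + c + d, the chance of an observed recurrence averaged over 5 to 11 years is

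(λ/L) × [1 − (e^(−5L) − e^(−11L))/(6L)].

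This is 0.1695 (SCRT) and 0.1005 (RCT), so expected events E = 380 × (0.1695 + 0.1005) = 102.6.

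- Schoenfeld: Φ(√E·|ln HR|/2 − 1.96) = Φ(10.13 × 0.2831 − 1.96) = 81.8%.
- Freedman: Φ(√E·(1−HR)/(1+HR) − 1.96) = Φ(10.13 × 0.2758 − 1.96) = 79.8%.

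So 760 patients and 80% power are recovered without any death term. Removing 10% of patients at the outset instead of using a loss hazard gives about 100 events and 81% (Schoenfeld), so this choice hardly matters.

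**Step 3. Add deaths, with 12% and 7% read as net rates.** For m = 20%, d = 0.04463 and E = 380 × (0.1435 + 0.0848) = 86.7. Power is 72.8% (Freedman) to 75.1% (Schoenfeld).

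**Step 4. Add deaths, with 12% and 7% read as crude incidences.** The hazards are now solved so that the cumulative incidence at 5 years equals 12% and 7%. For m = 20% they are 0.02867 and 0.01624 (HR 0.566). E = 96.3, and power is 77.5% to 79.6%.

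| Assumed 5-year death without recurrence | Events, net | Power, net | Events, crude | Power, crude |
|---|---|---|---|---|
| none | 102.6 | 79.8–81.8% | 102.6 | 79.8–81.8% |
| 10% | 94.6 | 76.5–78.6% | 99.4 | 78.7–80.7% |
| 20% | 86.7 | 72.8–75.1% | 96.3 | 77.5–79.6% |
| 30% | 78.9 | 68.8–71.0% | 93.1 | 76.3–78.5% |
| 40% | 71.1 | 64.3–66.5% | 89.8 | 75.0–77.2% |

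**Step 5. What 1 minus Kaplan-Meier would show.** Cumulative incidence at 5 years is λ/(λ+d) × [1 − e^(−5(λ+d))]. For m = 20%:

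- SCRT: 0.02557/0.07020 × (1 − 0.88 × 0.80) = 0.3642 × 0.296 = 10.8%.
- RCT: 0.01451/0.05914 × (1 − 0.93 × 0.80) = 0.2454 × 0.256 = 6.3%.

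| Assumed death | Cumulative incidence behind a Kaplan-Meier 12% v 7% | Difference, points |
|---|---|---|
| 10% | 11.4% v 6.7% | 4.75 |
| 20% | 10.8% v 6.3% | 4.5 |
| 30% | 10.1% v 5.9% | 4.2 |
| 40% | 9.5% v 5.5% | 4.0 |

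**The case against.** The strongest reply is that the Kaplan-Meier sentence speaks of survival. Overall and disease-free survival are endpoints, and Kaplan-Meier is right for them. No section says that recurrence will be reported as 1 minus Kaplan-Meier with deaths censored. This is a condensed article, and the choice of a descriptive estimator is commonly left to an analysis plan. That stands. A reader might infer that the trial's recurrence rates will be overstated, because the sentence sits between the primary endpoint and its tests and no other estimator is named. The documents support this only as a possibility.

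Three other strong readings also fail.

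- **The primary test is wrong.** It is not. Log-rank and Cox with deaths censored validly compare cause-specific hazards of recurrence.
- **Recurrences are overcounted.** Observed recurrences are not. Only the planned number may be too high.
- **The bias differs between arms.** That needs unequal mortality. The abstract's discussion cites similar long-term survival for both concepts, from non-comparative studies. With equal mortality both rates shrink by nearly the same factor (10.8/12 = 6.3/7 = 0.90 at 20% death), so the relative effect is almost unchanged.

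On power, the reply is that the mortality range has no source in the document and that the large losses arise only if 12% and 7% are net rates. Both points are correct. On the crude reading with 10% death, power cannot be told apart from the stated 80%. If the 10% loss was meant to include deaths, an allowance exists but is not labelled as one.

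What survives does not depend on an absent analysis plan. The planning inputs are printed here, none of them is a death rate, and they reproduce 760 without one.

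**Conclusion.** The point holds in a limited form. The sample size has no stated allowance for death without recurrence, and the article does not say whether its rates or its loss figure absorb it. Across 10% to 40% assumed death, expected recurrences fall from about 103 to between 95 and 71 on the net reading, or between 99 and 90 on the crude reading. The most that power loses is about 15 points (net, 40% death). The least is about 1 point (crude, 10% death).

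The overstatement of 5-year rates is conditional on recurrence being shown as 1 minus Kaplan-Meier. It would then be 0.6 to 2.5 points in the SCRT arm, 0.3 to 1.5 points in the RCT arm, and 0.25 to 1.0 point in the difference.

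These sizes rest on constant hazards, equal mortality in both arms, a mortality range that the document does not give, and counting recurrences for 5 to 11 years per patient, the horizon on which 760 is recovered. How that horizon fits a 5-year endpoint is a separate question and adds no weight here.

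**What to change.** - Estimate and plot local recurrence by cumulative incidence (Aalen-Johansen), with death without local recurrence as the competing event. Report the 5-year difference with its 95% confidence interval.
- Keep log-rank and Cox as the primary test, and describe it as a cause-specific comparison. Keep Kaplan-Meier for overall and disease-free survival.
- State whether 12% and 7% are net or crude rates, and whether the 10% loss includes deaths.
- Restate expected recurrences and power with a stated death rate.

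The cost is some wording and one extra analysis, with no change to treatment or data collection. The reported rates and the restated power may look slightly less favourable.

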### Surgery and histopathological analysis

Surgical resection has to be done within 5 days after SCRT or 5–6 weeks after the completion of RCT. The standard surgical procedure is total mesorectal excision (TME), for tumours located 10 cm above the anal verge a partial mesorectal excision (PME) is feasible; anterior resection, intersphincteric resection or abdominoperineal resection is done according to clinical staging and patient's preference. Quality (completeness) of TME has do be evaluated and documented by every surgeon at the resected specimen (by injection of methylene blue into the arteria rectalis superior).

The surgical specimens are processed and evaluated by standardized pathology and including UICC TNM categories and staging groups, number of examined and involved lymph nodes and the status of resection margins. In addition, the CRM (circumferential resection margin) and the TME-quality have to be documented by the pathologist according to the British Medical Research Council [15]. Histopathological response is deduced from tumour regression (TRG). TRG is evaluated according the 5 point scoring system of Dworak [16].

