### Adjuvant chemotherapy and follow-up

2–4 weeks after complete resection continuous 5-FU infusion therapy with 300 mg/m^2 ^BSA is applied for 12 weeks as far as there is no contraindication as serious impaired wound healing or anastomotic leakage. Toxicity will be evaluated during the chemotherapy and at follow-up.

Patients are included into a standardized follow-up program according to the guidelines of the Tumorzentrum Berlin. This includes follow-up visits at 3, 6, 12, 18 and 24 months after surgery, and then every year for a total of 5 years. Each visit includes physical examination, abdominal ultrasound, rectosigmoidoscopy and endorectal ultrasound (in case of sphincter saving surgery), CEA level as well as a chest X-ray every year. In addition, pelvic CT (or MRI) -scans are performed 3 months, 12 months, 24 and 36 months after surgery. Furthermore a complete colonoscopy is required 18 months, 36 months and 60 months post treatment.

Radiotherapy-related toxicities will be assessed during every visit using the LENT SOMA criteria.

Evaluation of quality of life is assessed by the EORTC QLQ D30 and QLQ D 38 questionnaire at time of randomisation, end of therapy, 3 and 6 months, 1 year, 3 years and 5 years after surgery.

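### Log-rank and Cox are assigned to the secondary endpoints without restriction, yet these include two yes/no outcomes fixed at surgery and repeated quality-of-life scores, which those methods do not suit

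*Protocol article*

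**What the plan says.** The Statistics section names one pair of methods: "Univariate Log-Rank tests as well as multivariate Cox' regression analyses will be conducted for the analysis of primary and secondary endpoints". It makes no exception, and the article names no other test for any endpoint.

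Study objectives lists overall survival, disease-free survival and quality of life as secondary outcomes. It then adds that "secondary endpoints are the complete resection rate (R0 resection) and the rate of sphincter saving resection", "both analysed after surgery of the last patient recruited".

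The time of surgery depends on the arm. The section on surgery states: "Surgical resection has to be done within 5 days after SCRT or 5–6 weeks after the completion of RCT". The Abstract gives the RCT interval as "plus TME-surgery 4–6 weeks later". For quality of life, the follow-up section states: "Evaluation of quality of life is assessed by the EORTC QLQ D30 and QLQ D 38 questionnaire at time of randomisation", with further assessments at the end of therapy, 3 and 6 months, and 1, 3 and 5 years.

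**The concern.** R0 and sphincter-saving resection are questions of whether, not when. Log-rank and Cox compare hazards, so they need a time origin, an event and a censoring rule, and the article gives none of these for the two outcomes. If time runs from randomisation, patients reach surgery at quite different times by design. The test can then respond to the schedule instead of the rates. Quality-of-life scores have no event time at all.

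The sphincter-saving comparison is prominent. The Background and the Abstract's discussion both offer the trial as a source of valid evidence on whether RCT permits less aggressive surgery, and planned resection type is a stratification factor. No suitable analysis is named for it.

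**Working it through.** **1. The plan's own figure.** The article gives a figure only for the primary endpoint: 760 patients, for local recurrence of 12% v 7% at 5 years. The hazard ratio is ln(0.93)/ln(0.88) = 0.568.
- Schoenfeld: 98 events. With 6 years of accrual and 5 of follow-up, the mean event probability is 0.1468, so 98/0.1468 = 668, and 668/0.9 = 742.
- Freedman: 104 events. With exponential loss of 10% per 5 years, the event probability is 0.135, so 104/0.135 is about 771.

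Both are within 3% of 760, so the figure reproduces and is not at issue. It gives 380 per arm if allocation is 1:1 (assumed). There is no figure for the resection endpoints.

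**2. When surgery falls.** Days from the start of radiotherapy:
- SCRT: a 5-day course, then surgery 1 to 5 days later: days 6 to 10.
- RCT: 28 fractions at 5 a week is 5 weeks plus 3 days, 38 days. Adding 28 to 42 days gives days 66 to 80. An interval of 5 to 6 weeks gives days 73 to 80.

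With an assumed wait of 0 to 28 days from randomisation to radiotherapy, SCRT surgery falls on days 6 to 38 and RCT surgery on day 66 at the earliest. The arms do not overlap. Log-rank uses only the order of times, so the choice between 4–6 and 5–6 weeks makes no material difference here.

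**3. Log-rank at equal true rates.** Simulation with 380 per arm, two-sided 5%, 800 runs per scenario and assumed success rates of 60% to 95%:

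| Origin | Event | Patients without the event | Rejection |
|---|---|---|---|
| Randomisation | Success | Censored at surgery | 100% |
| Randomisation | Success | Censored late | 99–100% |
| Randomisation | Failure | Censored at surgery | 100% |
| Randomisation | Failure | Censored late | 5–6% at 90–95% success; 11% at 80%; 24–26% at 70%; 60–64% at 60% |
| Surgery | Either | Either | about 4–6% |

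In a separate simulation (success as the event, from randomisation, treatment starting 3 to 14 days later), RCT was truly 10 points better, at 70% v 80% or 80% v 90%. Log-rank significantly favoured SCRT in 100% of runs.

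**4. Cox counted from surgery.** All times are then tied. With n patients and d events, the log-rank variance carries the factor (n−d)/(n−1). Breslow's approximation omits it, so the test statistic shrinks by about √(1−d/n). Take success as the event:
- 70% v 80%: pooled rate 0.75, z = 0.10/√(2×0.75×0.25/380) = 3.18. The shrinkage is √0.25 = 0.50, so z must exceed 1.96/0.50 = 3.92. Power is P(Z > 0.74) = 23%, against P(Z > −1.22) = 89% for two proportions.
- 80% v 90%: pooled rate 0.85, z = 3.86. The shrinkage is √0.15 = 0.387, so the threshold is 5.06. Power is about 11%, against 97%.

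Simulation agrees: 23% and 11% with Breslow ties, with almost no rejections at equal rates; 86% and 96% with Efron ties; 88% and 98% for two proportions. With failure as the event the Breslow loss is small. For 70% v 80% the shrinkage is √0.75 = 0.866, the threshold is 2.26, and power is P(Z > −0.92) = 82%.

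**5. Quality of life.** No calculation applies. The data are scores at seven planned occasions, including randomisation, and a hazard is not defined for them.

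**The case against.** The sentence sits between one on Kaplan-Meier survival estimates and one on hazard ratios changing over time. Its authors may have had only local recurrence, disease-free survival and overall survival in mind; the last two are secondary endpoints. Study objectives calls the resection outcomes rates and has them analysed once the last patient has had surgery, which suggests simple proportions. The article is condensed, and tests for binary endpoints are often left to the full protocol or SAP.

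Much of this stands. The narrower intention is plausible, and not naming a test of proportions would be no fault in itself. But the sentence is not silent. It assigns methods to the secondary endpoints, and a SAP that compared proportions would depart from it.

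A reader might infer that the plan as written will almost certainly declare the resection rates different. The article does not support that. It does not say that time runs from randomisation, that success is the event, or how other patients are censored. It states no null hypothesis for these two endpoints, and it does not say that the methods cover every secondary endpoint. Counted from surgery, log-rank is simply a comparison of proportions and keeps its level.

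**Conclusion.** Wrong as written; minor severity. The stated methods do not suit R0 resection, sphincter-saving resection or quality of life. The size depends on choices that the article leaves open. For log-rank, false rejection ranges from about 5% (from surgery, or failure as the event with few failures and late censoring) to about 100% (from randomisation with success as the event). The upper figure is a conditional worst case, not a property of the plan. For Cox from surgery the risk is lost power: about 23% instead of 88% for 70% v 80%, with Breslow ties and success as the event.

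These figures assume 1:1 allocation, success rates of 60% to 95% and a wait of at most 28 days before radiotherapy. None of these is in the article. The mismatch between method and endpoint does not depend on them.

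**What to change.** In Statistics, limit log-rank and Cox to local recurrence, disease-free survival and overall survival. Compare R0 and sphincter-saving resection as proportions among randomised patients: risk difference with 95% confidence interval, from a Mantel-Haenszel or logistic analysis using the stratification factors. Analyse quality of life with a repeated-measures model adjusted for the score at randomisation, which is already collected.

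The cost is a change of wording and standard analyses of data already planned, with no added patients or procedures. Separately, the RCT-to-surgery interval differs between the Abstract and the section on surgery, and the two must be reconciled.

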### Randomisation and stratification

Randomisation is done centrally at the clinical trial office of the Charité Comprehensive Cancer Center, Charité, Berlin. During randomisation patients are stratified by centre, tumour location (below 3 cm, between 3 and 8 cm, or between 8 and 12 cm above dentate line), TN-stage (uT2N+, T3N0, T3N+), open vs. laparoscopic surgery, and the type of resection (abdominoperineal resection vs. low anterior resection) according to the surgeons evaluation prior to preoperative therapy. Minimization has been used to ensure a balanced distribution with respect to arms and strata [13].

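### Two analyses are named for local recurrence without saying which decides, and neither is tied to the minimisation factors; adjusting for them would cost little and may recover up to a few points of power

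*Protocol article*

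**What the plan says.** All of this is in the protocol article.

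- Statistics, endpoint: "Local recurrence after five years follow up has been chosen as primary endpoint".
- Statistics, methods: "Univariate Log-Rank tests as well as multivariate" Cox regressions are planned for the primary and the secondary endpoints alike. The two methods stand side by side. Neither is called primary, and the covariates of the Cox model are not listed.
- Statistics, sample size: the calculation assumes "expected local recurrence rates of 12% in the SCRT arm compared with 7% in the RCT arm", "resulting in altogether 760 patients (Log-Rank-test", two-sided 5%, 80% power, 10% loss per arm). Alpha and power are attached to the log-rank test alone.
- Randomisation and stratification: the factors are centre, tumour location (three levels), TN-stage (three), open or laparoscopic surgery (two) and planned type of resection (two). "Minimization has been used to ensure a balanced distribution with respect to arms and strata".

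No section says that either analysis will, or will not, take account of these factors.

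**The concern.** Minimisation makes the arms more alike on the chosen factors than simple randomisation would. If those factors predict local recurrence, the treatment comparison varies less from trial to trial than an unadjusted log-rank assumes. Its standard error is then too large, it rejects slightly too seldom under the null, and it loses power. Leaving prognostic covariates out also pulls the estimated hazard ratio towards 1. An analysis that includes the factors avoids both.

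The second issue is ranking. With two analyses of one primary endpoint and no stated order, a reader of the article cannot tell which result will be the trial's answer, and the choice could be made after both are known.

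**Working it through.** **1. The plan's own figure.** Exponential hazards from the five-year rates:

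- SCRT: −ln(0.88)/5 = 0.02557 per year
- RCT: −ln(0.93)/5 = 0.01451 per year
- hazard ratio: 0.01451/0.02557 = 0.568

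Schoenfeld events: 4 × (1.960 + 0.842)² / (ln 0.568)² ≈ 98. With uniform accrual over 6 years and 5 further years of follow-up, the event probability per arm is 1 − (e^(−5λ) − e^(−11λ))/(6λ). This gives 0.184 and 0.109, mean 0.1468. Then 98/0.1468 = 668 patients, and 668/0.9 = 742. The Lachin–Foulkes formula with 10% lost by five years gives 762. The stated 760 is therefore an unadjusted log-rank design, with 1:1 allocation assumed because no ratio is stated.

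**2. Mechanism.** Let R be the share of the log-rank variance that comes from differences between factor levels. If allocation balances the factors fully, the null standard deviation of the statistic is about √(1 − R), so the true size is about 2Φ(−1.96/√(1 − R)). A size of 4.5% (critical value 2.005) corresponds to 1 − R = (1.96/2.005)² = 0.956, so R is about 4%. A size of 4.0% (2.054) gives 0.911, so R is about 9%. With R = 0 nothing is lost.

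**3. Simulated size and power.** All runs use 760 patients, the planning hazards and biased-coin minimisation. Factor effects, prevalences, number of centres and coin probability are assumptions, because the article gives none of them.

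- A: 12,000 runs per cell, coin 0.8, five factors, 15 centres, 6 years' accrual plus 5 years' follow-up (about 100 events). Moderate: HR 1.5 per location step, 2 for T3N+, 1.5 for abdominoperineal resection, centre SD 0.3. Strong: 2, 3, 2 and 0.5.
- B: 4,000 runs, coin 0.9, four factors, five years per patient, 10% loss. HR 2/1/0.5 for location, 0.5/0.6/1.5 for TN-stage, 1.3 for planned abdominoperineal resection; then log effects × 1.5.
- C: 6,000 runs, coin 0.8, four factors, five years per patient, 10% loss (about 65–68 events). Moderate clinical effects as in A; then log effects × 1.7.

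| Set | Factor effects | Size, log-rank / adjusted Cox | Power, log-rank / adjusted Cox | Gain (points) |
|---|---|---|---|---|
| A | none | 5.1% / 5.0% | 81.3% / 81.1% | −0.2 |
| A | moderate | 4.5% / 5.0% | 78.0% / 78.6% | 0.6 |
| A | strong | 4.0% / 5.0% | 72.4% / 75.3% | 2.9 |
| B | base | 4.6% / 5.6% | 58.8% / 60.2% | 1.4 |
| B | × 1.5 | 3.5% / 4.9% | 56.3% / 61.3% | 5.0 |
| C | moderate | 4.5% / 4.8% | 61.5% / 62.3% | 0.8 |
| C | × 1.7 | 4.3% / 5.3% | 57.8% / 61.1% | 3.3 |

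The Monte Carlo standard error of a 5% size is √(0.05 × 0.95/12,000) = 0.2 points in A and about 0.35 in B. Set A resolves the conservatism under strong effects (4.0%). The base case of B (4.6%) does not by itself.

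The power levels differ because A follows early patients for up to 11 years, while B and C stop at five years. The gain from adjustment is similar on both readings.

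**4. Taking the better of the two tests.** In set C this gave a type I error of 5.0–5.7% with a fixed covariate set. A free choice of covariates could add more.

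**5. Full stratification.** The factors make 3 × 3 × 2 × 2 = 36 cells per centre, or 36 × 15 = 540 cells for about 100 events. In set A the power of a log-rank stratified on every cell was about 54%, 51% and 47% (no, moderate and strong effects).

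**The case against.** A reader might infer more: that the unadjusted log-rank is the primary test, and that it is therefore conservative and underpowered because of minimisation. The article does not support this.

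- The sentence that names the log-rank also names multivariate Cox regression for the primary endpoint. Sizing a trial on a log-rank test is routine even where an adjusted model decides.
- Nothing says that the Cox model leaves the minimisation factors out. A condensed article commonly leaves the covariate list and the ranking to the full protocol or SAP, which may already contain the analysis proposed here.
- Conservatism is conditional. Without prognostic effects there is none, and with moderate effects the loss is 0.6 to 1.4 points. The largest gain needs extreme assumptions: the base effects in set B already span (2/0.5) × (1.5/0.5) × 1.3 = 15.6-fold in hazard between best and worst patient, and about 62-fold after scaling (15.6^1.5).
- In the base case of B, the Cox model also rejected 1.0 point more often under the null, so its 1.4-point power gain is not a clean comparison.
- The error of the log-rank is on the safe side.

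All of this stands, and it limits the point to efficiency and clarity. It does not remove the point. The one test that carries the design's alpha and power is unadjusted, patients are allocated on five named factors, and the article describes its analysis without joining the two or ranking its methods.

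**Conclusion.** The point holds in a limited form. The article leaves open which of two analyses decides the primary endpoint, and it ties neither to the minimisation factors. If the log-rank decides, the cost in power is about 0 points with non-prognostic factors, under 1 to 1.5 with moderate ones and about 3 to 5 with strong ones. These figures rest wholly on assumed prognostic strengths. The direction is well supported where the factors are prognostic; the size is not known.

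The log-rank's simulated size lies between 3.5% and 5.1%, so type I error is not inflated and a positive result would not be in doubt on this ground. Choosing between the two analyses after the fact adds little with fixed covariates, but the article sets no limit on the covariates. The full protocol or SAP may already settle both matters.

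**What to change.** State, before any comparative data are examined (the planned interim analysis included), that the single decisive analysis of local recurrence is a main-effects Cox model. It should contain treatment, tumour location (three levels), TN-stage (three), open or laparoscopic surgery and planned resection, with centre as a random effect or grouped by size. Keep the univariate log-rank as supportive. Do not stratify a log-rank on all factors including centre. If the full protocol or SAP already says this, a cross-reference is enough.

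The clinical covariates take 2 + 2 + 1 + 1 = 6 parameters, plus one for treatment. At 98 events that is 98/7 = 14 events per parameter, and at 65 events about 9, so the model is workable on either reading of follow-up.

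The cost is wording only, because every factor is recorded at randomisation and the sample size need not change. The small downside is that the hazard ratio becomes conditional on the factors, so it is not the same quantity as the unadjusted ratio behind the 12% and 7% planning rates. Reporting the Kaplan–Meier estimates and the univariate test beside it covers this.
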